## Abstract

**Background:**

In Scotland a new, easier to complete bowel screening test, the Faecal Immunochemical Test (FIT), has been introduced. This test gives more accurate information about an individual’s risk of having colorectal cancer (CRC), based on their age and gender, and could lead to fewer missed cancers compared to the current screening test. However, there is no evidence of the effect on colonoscopy uptake of providing individuals with personalised risk information following a positive FIT test.

The objectives of the study are:To develop novel methods of presenting personalised risk information in an easy-to-understand format using infographics with involvement of members of the publicTo assess the impact of different presentations of risk information on informed choice and intention to take up an offer of colonoscopy after FITTo assess participants’ responses to receiving personal risk information (knowledge, attitudes to screening/risk, emotional responses including anxiety).

**Methods:**

Adults (age range 50–74) registered on the Scottish Bowel Screening database will be invited by letter to take part. Consenting participants will be randomised to one of three groups to receive hypothetical information about their risk of cancer, based on age, gender and faecal haemoglobin concentration: 1) personalised risk information in numeric form (e.g. 1 in 100) with use of infographics, 2) personalised information described as ‘highest’, ‘moderate’ or ‘lowest’ risk with use of infographics, and 3) as a ‘positive’ test result, as is current practice. Groups will be compared on informed choice, intention to have a colonoscopy, and satisfaction with their decision. Follow-up semi-structured qualitative interviews will be conducted, by telephone, with a small number of consenting participants (*n* = 10 per group) to explore the acceptability/readability and any potential negative impact of the risk information, participants’ understanding of risk factors, attitudes to the different scenarios, and reasons for reported intentions.

**Discussion:**

Proving personalised risk information and allowing patient choice could lead to improved detection of CRC and increase patient satisfaction by facilitating informed choice over when/whether to undergo further invasive screening. However, we need to determine whether/how informed choice can be achieved and assess the potential impact on the colonoscopy service.

**Trial registration:**

The trial is registered on www.isrctn.com on 08/12/2017. Registration no: ISRCTN14254582.

## Background

In Scotland, the guaiac Faecal Occult Blood Test (gFOBT) has recently been replaced by a quantitative Faecal Immunochemical Test for haemoglobin (FIT) in the bowel cancer screening programme, after a successful demonstration pilot of “FIT as a First-Line Test”. FIT will initially be used with a faecal haemoglobin concentration of 80 μg Hb/g faeces in order to achieve approximately 2% positivity, to mimic the screening algorithm based on the previous two-tier reflex gFOBT/qualitative FIT strategy. However, FIT (along with age/gender) could provide a more personalised risk of harbouring advanced neoplasia (colorectal cancer (CRC) or high risk adenoma), and thus empower people to make an informed decision about whether or not to undergo colonoscopy, by balancing the risks of the procedure (e.g. bleeding/bowel wall perforation) against the risk of missing a cancer. This is particularly important in CRC screening. Currently, about half of all cancers in the screened population are diagnosed in the interval between screening rounds, indicating that, at the current threshold, the test is only about 50% sensitive for colorectal cancer. Reducing the threshold would result in fewer cancers being missed but would increase the chance of a negative colonoscopy and the impact on the colonoscopy service may be unsustainable. Thus, we aim to investigate the potential implications of providing the screened population with a more informed choice to help establish the impact on colonoscopy services.

This early phase study aims to assess patient responses to personalised risk information about their estimated risk of having colorectal cancer. Screened participants will be randomised to receive hypothetical scenarios of personalised risk information based on age, gender and haemoglobin concentration; or to treatment as usual, i.e. a positive/negative test result based on approximately 2% positivity (i.e. the proportion of screened individuals with a positive result). The best methods to present this information will be determined by this study. Study arms will be compared on level of informed choice achieved and intention to undergo colonoscopy and satisfaction with the decision made. Thus, we will assess the potential impact on colonoscopy services of introducing personalised risk information and whether informed choice can improve patient outcomes/satisfaction. The results will be used to inform a full-scale randomised controlled trial (RCT) to evaluate uptake of colonoscopy for Scottish Bowel Screening programme participants. The intervention could be low-cost to deliver at scale, and thus prove cost-effective for introduction within the national screening programme.

In order to inform a large population-based study, we must first assess the optimal method of delivering information for a truly informed choice. There is a dearth of current evidence. A recent Cochrane systematic review examined the effect of personalised risk communication for informed decision-making in uptake of medical screening compared to general information [1]. Overall, providing a numerical risk score or a categorised risk (e.g. ‘low’, ‘medium’, ‘high’) increased informed choice (odds ratio: 3.65 (95% C.I. 2.13 to 6.23), for random effects and screening uptake (odds ratio: 1.15 (95% C.I. 1.02 to 1.29)). However, the included studies covered a wide range of screening tests and thus the results were heterogeneous. Of the studies involving CRC, only one used a calculated numerical risk score, leading to greater knowledge but non-significant *lower* intention and uptake; it did not report changes in informed choice [2]. Three studies used a categorised risk score; these did not assess knowledge or informed choice, but indicated a small, significant increase in uptake of screening [3–5]. The authors concluded that the evidence that personalised risk communication increases screening uptake is weak. Further, although some included colonoscopy, all of the reviewed studies involving CRC screening related to first line screening only.

There is thus no existing evidence on the effects of personalised risk information on uptake of colonoscopy following first line screening for CRC. Our study would fill this knowledge gap. It will develop a novel personalised risk information intervention to enable national bowel screening programme participants to make an informed choice about having a colonoscopy following a FIT result with detected haemoglobin, by weighing their personalised risk versus the risks/disadvantages of colonoscopy. The proposed study has the potential to: 1) provide individuals with truly informed choice based on their own risk level, 2) reduce the number of ‘missed’ interval cancers by offering colonoscopy at lower thresholds than the current cut-off, 3) improve patient outcomes and satisfaction. We will determine the best methods for achieving informed choice and, if successful, they would have the potential to be extended to other screening/treatment scenarios, and thus have much wider impact. The study outcomes would give indicative effects to inform a larger RCT designed to provide evidence on any impact on colonoscopy services.

This research will deliver new knowledge about the impact of personalised risk information on delivering informed choice for colonoscopy and has the potential to benefit NHS managers and policy makers, cancer charities, members of the public, behavioural scientists and academics interested in health behaviour and informed choice.

Providing patients with informed choice is a core NHS tenet yet there is little evidence on its impact on CRC screening uptake. We believe this research could lead to improved detection of CRC, improve health outcomes and save lives. If results are promising, it would be feasible to present risk information in the format(s) developed in this research project within the scope of the Scottish bowel screening programme in the future. Thus it has the potential to increase patient satisfaction by helping them to make their own informed decision over when or whether to undergo invasive screening. Although there could be increased costs to the NHS due to increased colonoscopy uptake; earlier cancer detection could ultimately reduce NHS treatment costs and would contribute towards meeting the aim of the Detect Cancer Early Programme to improve 5-year survival.

In the longer-term, the intervention could be adapted for other settings where individualised information may be available including medical screening, treatment decisions and in promoting lifestyle changes to reduce future health risks, and so it has the potential for much wider impact. It is proposed that any follow-up study should include GP interactions, as patients receiving a positive FIT result may seek advice from their GP in making an informed decision about colonoscopy.

The aims of this study are:To develop methods of presenting personalised risk information to Scottish Bowel Screening Programme participants, in an easy-to-understand format using infographics.To assess the impact of different presentations of risk information on informed choice and intention to take up an offer of colonoscopy after FIT.To assess participants’ responses to receiving personal risk information, including knowledge, attitudes to screening and risk, and emotional responses including anxiety.

## Methods

A simple 3-arm RCT design will be used for an intervention to present different levels of personalised risk and its effect on informed choice and intention to take up an offer of colonoscopy. The three groups are: 1) numerical personalised risk information, 2) categorical risk information, 3) positive screening test result. This is a single centre study covering the whole of Scotland and based at NHS Tayside, Ninewells Hospital & Medical School in Dundee.

Table 1 lists the objectives, hypothesis and variables, analysis techniques and anticipated conclusions of the study.

**Table 1 Tab1:** Study Matrix

Objective	Hypothesis	Variables	Techniques of analysis	Anticipated Conclusions
1) Level of informed choice (derived from knowledge, attitudes, informed subscore of Decisional Conflict Scale). 2) Development of novel, personalised risk information materials. 3) Intention to take up an offer of colonoscopy.	Providing personalised risk information will provide individuals with truly informed choice based on their own risk level and improve satisfaction in screening participants.	• Age • Gender • SIMD • Study arm • Previous screening history • Measures of informed choice: ° Knowledge ° Attitude ° Informed subscore (Decisional Conflict Scale) • Behaviour (intention to uptake colonoscopy) • Anxiety	Comparison of knowledge, attitudes and intention to uptake colonoscopy between the study arms. Data on intention to take up colonoscopy from each scenario will be matched with the expected range of risk scores in the Scottish population. Comparison of themes from the qualitative analysis between those who intended and did not intend to take up the offer of colonoscopy. Any differences with respect to age/gender/ socioeconomic status and also whether or not previously participated in screening and/or taken up the offer of colonoscopy would also be explored.	Differences in intention to uptake colonoscopy between study arms will help to inform a full-scale RCT to evaluate uptake of colonoscopy in Scottish Bowel Screening Programme participants.

*SIMD* Scottish Index of Multiple Deprivation

Recruitment will be carried out by the Research Fellow (RF). Adults registered on the Scottish National Bowel Screening Programme database (age range 50–74 years) will be purposely selected to represent all age ranges, all deprivation categories and both genders as these factors have been shown to be associated with screening uptake. As it is typical in questionnaire-based research to get more responses from some groups (e.g. older people and higher socio-economic groups), the target recruitment will be weighted towards those groups who may be less likely to participate, based on response levels obtained from our large-scale questionnaire study on bowel screening [6], with the aim of achieving a balanced sample of participants.

Prospective participants would be approached, by letter, sent on behalf of the Principal Investigator (PI), Director of the Scottish Bowel Screening Programme, to ask if they would like to participate in a survey to assess their response to an offer of colonoscopy in relation to an estimated personalised risk of having cancer. A full patient information sheet and a response form will be included along with a pre-paid envelope for return. In line with published criteria for increasing recruitment [7], we would use techniques including personally addressed invitation letters, signed by the PI, stamped rather than franked return envelopes, and coloured ink. The participants would also be asked whether or not they would consent to taking part in a short follow-up interview by telephone. A response form will give the option to provide a telephone number if they are happy to being contacted in this way along with the postal address to receive the study risk materials with the questionnaire. Those not replying are assumed to have declined to participate. On receipt of the returned completed response form, it would be considered that the patient is in the study and would be randomised to receive the study materials. Return of the completed questionnaire will be considered as an implied consent.

Verbal consent will be confirmed at the start of the telephone interview, including consent for audio-recordings. The consent form will be read and audio recorded along with patient replies which will also be ticked on paper. Participants can still take part in the telephone interview, even if they do not wish to be recorded, in which case responses would be recorded on paper. A study ID will be assigned prior to transcription to ensure the interview is anonymised. The consent form will be stored separately to the anonymised study data.

A designated contact person who is external to the study team has also been nominated if prospective participants wish to discuss any concerns that invitees may have regarding the study before giving consent. The Patient Information Sheet will make clear that participants may withdraw from the study at any time without giving a reason and their data will be removed from the study.

Based on previous research [8], it is expected that 25% will respond and be randomised, we expect a further 20% attrition between consent and questionnaire return.

The risk information materials will initially be pilot tested in around 30 participants from the screening database. Therefore, 144 will be invited, with 36 expected to respond and 30 completing the questionnaire.

Following the pilot testing in sample participants, a further 1440 will be invited to receive the finalised personalised risk information about their risk of having colorectal cancer and provide responses. As above, it is expected that 360 will respond and be randomised, with 300 then completing the study questionnaire. Figure 1 shows a flow diagram of the study design with expected numbers of participants. A small number of participants would be purposively sampled, from those consenting to be telephoned, from each treatment arm, estimated at 10 per arm, total = 30, to provide representation with regard to age, gender, socioeconomic status and responses to the scenarios.

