Presentation or risk will be assessed both as a ‘1 in x risk’ and natural frequencies in the development process, one or both of these may be used in the final materials. Participants will also be presented with the information on the risks of having a colonoscopy which is currently provided to those who are offered the test following a positive gFOBT. Group 3 is effectively a control group, which reflects current practice, to allow comparison of likely uptake of colonoscopy with the personalised risk information groups. Three verbal categories (lowest, moderate, highest risk) for simplicity of presentation of information are proposed. However, it is possible this could be modified during the development process, if the PPI involvement suggests otherwise. The development of the risk materials is a key part of the project, thus it is not possible to be too specific on detailed content or categorisations at this stage. The finalised risk materials will be used in the RCT across Scotland.

Patients who complete and return the response form indicating that they are willing to take part will be randomised to one of the study arms and then posted the materials and informed choice questionnaire with a stamped addressed envelope for return of the questionnaire. Study documents which will be sent to the participant are: Scenario letter(s) according to study arm, study questionnaire, “Having a colonoscopy” leaflet and “The Bowel Screening Test” leaflet. Return of the questionnaire will be considered as an implied consent.

Randomisation with minimisation on variables related to risk (i.e. age, SIMD, gender) will be carried out via MINIM software by an individual independent to the process of running the study, who will thus be blinded to the recruitment process.

The study will be co-ordinated by a Study Management Group, consisting of the PI, Co-investigators, Research Fellow and two PPI members.

Consenting participants will be randomised to one of 3 conditions:Numerical (i.e. a personalised numerical-based risk assessment (e.g. 1 in x risk) related to hypothetical test result and age and gender)Categorical (as treatment group 1) but this would be categorised as ‘Lowest’, ‘Moderate’ and ‘Highest’ riskPositive cut-off (i.e. as current practice that is i.e. a positive test result, based on the current cut-off to give approximately 2% positivity).

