Each condition would be presented with hypothetical scenarios relating to different levels of risk of CRC and asked to rate their intention of attending a colonoscopy if they received that result following an actual FIT. Three scenarios, relating to lowest, moderate and highest risk for colorectal cancer would be presented in groups 1 and 2; by definition group 3 has only one possible scenario i.e. a positive screening test result.

The lowest, moderate and highest risk categories and the disease frequencies used in the scenarios will be derived from data from a study which observed that risk of significant colorectal neoplasia rises with increasing faecal haemoglobin concentrations [13]. Although the actual faecal haemoglobin concentrations might represent different risks for individuals (e.g. different genders), the hypothetical scenarios would be presented as a specific level of risk (e.g. with this result you would have a 1 in x risk (or a moderate risk) of having CRC) and thus would be applicable to all participants. The aim of using both actual numerical risks and verbal categories is to assess their impact on the understanding and reactions of participants to these different forms of materials. The standard information describing the first-line screening process will be provided as an introduction to the different scenarios, as participants may have different previous experiences of first line screening.

A study questionnaire will be used to collect participant responses to information materials including intention, knowledge about the test (8 items: including risks of having cancer and undergoing a colonoscopy) and attitudes towards undergoing the test (4 items: including benefits, importance and pleasantness/ unpleasantness) and anxiety. Questionnaire data will be collected at a single time-point (months 19–21). Telephone interviews will be conducted in a small number of participants (10 from each study arm) to collect more detailed responses.

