We will use the informed subscore (items 1–3) from the Decisional Conflict Scale [17] to assess the extent to which participants feel informed about their decisions. These items are: “I know which options are available to me”, “I know the benefits of each option” and “I know the risks and side effects of each option”, scored on a 7-point scale from “strongly agree” to “strongly disagree”. As this is a hypothetical scenario study we are only able to use intention and not actual uptake as our outcome measure of behaviour. However, intention was very strongly related to actual uptake (with a mean intention score of 6.7 out of a maximum 7 for kit returners) in our previous large-scale study [6].

*Intention* to take up the offer of colonoscopy, as a proxy for behaviour, will be measured on a Likert-type scale from 1 (low intention) to 7 (strongly intend) in response to e.g. “If I received information that I had *x* level of risk of bowel cancer, I would choose to have a colonoscopy”. *Anxiety* will be measured by a previously-validated six-item version of the State Trait Anxiety Inventory [18]. An example item is the statement “I am worried”, with a choice of four responses on a scale from “not at all” to “very much”.

Ease of understanding and acceptability of the presentation of risk information will also be assessed in the questionnaire using Likert-type questions e.g. “I found the information presented easy to understand” scored on a 7-point scale from “strongly agree” to “strongly disagree”.

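### As described, the invitation sent to everyone before randomisation announces personalised cancer-risk information that arm 3 does not receive, which may shift arm 3's self-rated outcomes or questionnaire return

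*Protocol article*

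**What the plan says.** The article's Methods section describes the approach to prospective participants. A letter asks them to take part in "a survey to assess their response to an offer of colonoscopy in relation to an estimated personalised risk of having cancer". The letter comes with other documents: "A full patient information sheet and a response form will be included along with a pre-paid envelope for return". Further on, where the expected numbers are set out, the article says "a further 1440 will be invited to receive the finalised personalised risk information about their risk of having colorectal cancer".

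Allocation comes after this: "On receipt of the returned completed response form, it would be considered that the patient is in the study and would be randomised". Arms 1 and 2 then receive three scenarios expressed as a numerical or a categorical risk. For the third arm, "by definition group 3 has only one possible scenario i.e. a positive screening test result". Its role is stated in the same section: "Group 3 is effectively a control group, which reflects current practice, to allow comparison of likely uptake of colonoscopy".

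The outcomes come from one postal questionnaire. They include a three-item informed subscore, used "to assess the extent to which participants feel informed about their decisions", together with attitudes, intention, a six-item anxiety scale, ease and acceptability of the information, and an eight-item knowledge measure. Return of the questionnaire counts as implied consent, and 20% attrition is expected between consent and return.

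**The concern.** A person who receives a positive result in the real programme has not first been told about a personalised risk estimate. A participant in arm 3, on the article's description, has been told exactly that and then receives none. The participant reads the material, so cannot be blind to what it contains, and then rates it and his or her own state of mind. Someone who expected a risk estimate may say that they feel less informed, or find the material less acceptable, partly because of what the letter led them to expect.

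The control arm carries a good deal of weight. It is the reference for informed choice, for intention, and for the projected load on colonoscopy services compared with the current cut-off. The article also intends the effect sizes to inform a full-scale trial, so an artefact in arm 3 would be carried into that trial's planning.

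**Working it through.** **1. The statements side by side (all from Methods).**

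- Before randomisation, all invitees: the survey is about an offer of colonoscopy in relation to personalised cancer risk.
- Before randomisation, all 1440: invited to receive personalised risk information.
- After randomisation, arms 1 and 2: a stated risk level in each of three hypothetical scenarios.
- After randomisation, arm 3: a positive result and no risk level.

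The statement about the 1440 cannot be true of those later allocated to arm 3.

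**2. Which part can bias a comparison.** Write the expected score in arm k as μ_k + s + e_k. Here μ_k is the score without the framing, s is the effect of the letter common to everyone, and e_k is the reaction to any gap between what was announced and what arrived. Then

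(arm 1) − (arm 3) = (μ_1 − μ_3) + (e_1 − e_3).

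The common effect s cancels. Only e_1 − e_3 remains. Nor is e_1 necessarily zero, because arms 1 and 2 receive hypothetical risk levels and not the participant's own risk. The gap is largest in arm 3, where no risk level of any kind is given.

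**3. Which outcomes are exposed.** The informed subscore, attitudes, anxiety, intention and acceptability are self-ratings. Knowledge is scored and is less exposed, except through who returns the questionnaire. Informed choice is described as combining knowledge and attitudes with either the informed subscore (Table 1) or behaviour, measured as intention (Methods text). Either way, two of its three components are self-rated. Of the two outcomes in the power statement, attitudes are exposed and knowledge less so.

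**4. The plan's own figure.** The article states 83.7% power with 100 per arm for a 1-point knowledge difference by one-way ANOVA. No SD or significance level is printed. Assuming 5%, the figure is returned by

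- SD 2.50 if both intervention arms lie 1 point above control;
- SD 2.17 if the three means are evenly spaced over 1 point;
- SD 2.40 for a two-sided pairwise comparison.

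It is attainable but cannot be confirmed, and this point does not dispute it.

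**5. Illustration of size (the shifts are assumptions).** With 100 per arm, the standard error of a pairwise difference in SD units is √(2/100) = 0.1414. The difference detectable with 80% power is 2.80 × 0.1414 = 0.396 SD. If there is no true effect and arm 3 is shifted by d, the chance of a two-sided 5% result is Φ(d/0.1414 − 1.96) + Φ(−d/0.1414 − 1.96):

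| Assumed shift d | Chance of a significant difference |
|---|---|
| 0.1 SD | 11% |
| 0.2 SD | 29% |
| 0.3 SD | 56% |

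A shift the other way costs power. Take a true pairwise effect with 83.7% power (1/2.40 = 0.42 SD). Narrowing it by a quarter leaves about 60%, and by a half about 31%.

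**6. Questionnaire return (the split is an assumption).** With 360 randomised, each arm has 120. An even 20% loss leaves 96 per arm, or 288. (The article gives 300, a separate matter that does not bear on this point.) A loss of 15%, 15% and 30% leaves 102 + 102 + 84 = 288, the same total. The overall return would look as planned, so only a comparison by arm would show the difference.

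**The case against.** The strongest reply is that the article paraphrases the letter in one clause, and that neither the letter nor the information sheet is shown. The sheet may explain that one of several formats is sent at random. That is fair: nothing here shows that the actual wording is faulty, and the absence of those papers is not a defect. The point rests on the invitation as the article describes it, twice and in the same sense.

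Three stronger readings are tempting, and the documents support none of them.

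- *That the letter biases the trial by attracting people who want risk information.* The letter reaches all arms before randomisation. Such selection and priming are shared; they may limit generalisability but do not by themselves bias the contrast.
- *That arm 3 is disappointed, so the benefit of arms 1 and 2 is inflated.* Disappointment is a plausible risk, not a reported fact. The scenarios are stressed as hypothetical, so nobody receives their own risk. Lower ratings and lower return need not add up, either: if the disappointed do not reply, those who remain are the less disappointed, which offsets the first effect. For intention, no direction follows.
- *That arm 3 does not represent current practice.* Its content, a positive result at the current cut-off with leaflets, does match it. What differs is the context in which it is read.

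What stands is the differential part: announced content that reaches two arms in form and the third not at all. A sheet that describes the formats would not necessarily remove this, since arm 3 might then recognise that it had the usual one.

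**Conclusion.** The point holds as a plausible differential-expectation bias, not a demonstrated one. The article describes a pre-randomisation invitation that does not fit what arm 3 receives, and most outcomes are self-ratings by people who see their own material. The size is unknown and the direction uncertain for some outcomes. The 0.1 to 0.3 SD shifts and the 15/15/30% split are assumptions without any anchor in the documents; they show only that a modest shift would matter with 100 per arm. The conclusion also assumes that the letter resembles the article's description of it. Calling arm 3 a reflection of current practice is right for its content and too strong for its context. The change is worth making because it is cheap and removes the mechanism at its source.

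**What to change.** Word the invitation and the information sheet neutrally and identically for all arms. For example: *a survey of how people respond to different ways of giving hypothetical bowel screening results and an offer of colonoscopy; you will be sent one version chosen at random, and some versions describe the chance of having bowel cancer*. The last clause should stay: the article recognises that thinking about cancer risk may disturb some invitees, and they need to be able to decline before the pack arrives.

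Correct the sentence on the 1440 so that it does not say all of them are invited to receive personalised risk information. Compare questionnaire return by arm.

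If the letters have already gone out, qualify the description of arm 3 as current practice when its results are interpreted, and give the invitation's framing as a limitation.

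The cost is a slightly less specific invitation and ethics approval of the new wording. No change in sample size follows.
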